### Sample size

The primary outcome will be the QuickDASH score of which the minimal clinically important difference is 14 points. Based on a difference of 14 points, the sample size of 30 patients per treatment group was calculated with a power (1-β) of 80 percent and a type I error (α) of 5 percent, allowing for 10 percent drop-out. In total 70 patients will be included.

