### Statistical analysis

#### *Descriptive statistics*

Data from the demographic data collection and the outcome parameters will be cleaned blindly from the treatment data. Data are presented as mean scores with 95% confidence intervals.

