#### *Univariate analysis*

The analysis of this study will be carried out according to the intention-to-treat principle, i.e. the patients will remain in the group they will be randomly allocated to at baseline. Analysis of functional outcome will be assessed using repeated-measures analysis of variance (GLM 4) with the time as the within-group factor and the treatment as the between-group factor. Post-hoc analysis will be performed on the time of randomization. Group comparisons at the different time points will be made only when the overall repeated-measures tests are statistically significant. All scores will be tested for normality using the Kolmogorov-Smirnov test. Parametric variables will be compared using the Student’s t-test, while non-parametric and ordinal variables will be compared using the Mann–Whitney U statistic. Nominal variables will be compared across independent groups using the chi-squared test or Fisher’s exact test. Homogeneity of variance will be assessed using Levene’s test. Also a multiple regression will be performed. SPSS statistical software (version 11.0.1) will be used for the analysis, in which two-tailed P value < 0.05 will be considered significant.

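### A normality pre-test lets the one-year QuickDASH comparison switch from means to ranks, although the trial is sized and reported on means

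*Protocol article*

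**What the plan says.** Three parts of the protocol article bear on this point.

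- **Univariate analysis.** Functional outcome is assessed by repeated-measures ANOVA with time and treatment as factors. Comparisons at single visits follow only if the overall test is significant. The section then states "All scores will be tested for normality using the Kolmogorov-Smirnov test". Student's t-test is assigned to parametric variables. The remaining scores fall under a second clause, "while non-parametric and ordinal variables will be compared using the", which names Mann–Whitney. The link from the normality result to the choice of test is carried by the order of the sentences, but the normality test is given no other purpose.
- **Sample size.** QuickDASH is named as the primary outcome, and its minimal important difference drives the calculation: "Based on a difference of 14 points, the sample size of 30 patients per treatment group was calculated". Power is set at 80% and alpha at 5%.
- **Descriptive statistics.** "Data are presented as mean scores with 95% confidence intervals".

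The abstract sets the primary assessment at one year. Outcome measures puts QuickDASH on a 0–100 scale on which higher is worse.

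**The concern.** The quantity compared at one year is left to the outcome data. A t-test compares mean scores. Mann–Whitney compares the chance that a patient in one arm scores lower than a patient in the other. If the pre-test sends QuickDASH to ranks, the p-value no longer concerns the 14-point difference on which the trial was sized, and it sits beside means and intervals that answer another question.

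The distinction could matter here. If early cast removal gave most patients a small gain and a few a large loss, ranks would register the many small gains and largely ignore how badly the few fared, whereas the mean would count both. The conclusion at one year could then depend on a preliminary test.

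**Working it through.** **1. The plan's own figure.** For two means, n per arm = 2 × (1.960 + 0.842)² × SD² / 14², and (1.960 + 0.842)² = 7.849. The article gives no SD, so 30 per group cannot be reproduced directly. Solving backwards:

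- 30 evaluable per arm: SD = 14 × √(30 / 15.698) = 19.35.
- If 30 already includes drop-out, 30 × 0.9 = 27 evaluable: SD = 14 × √(27 / 15.698) = 18.36.
- Drop-out: 30 / 0.9 = 33.3, so 34 per arm and 68 in total, close to the stated 70.

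The sizing is on a difference in points, and an SD near 19 fits it.

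**2. Is skew plausible at one year?** The article gives no expected mean. Assume 20. A normal distribution with SD 19.35 would put Φ(−20 / 19.35) = Φ(−1.03) = 15% of scores below 0, which the scale does not allow. A lower mean makes this worse. The Background describes excellent results in most non-operatively treated patients, and the abstract mentions lasting restrictions in up to 30%. Together these suggest many low scores and a right tail.

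**3. How often would the pre-test reject?** Simulated, 60 patients pooled, all shapes assumed:

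| Shape | Mean, SD | Lilliefors | Uncorrected |
|---|---|---|---|
| Skewed, many zeros | 10.4, 14.1 | 1.00 | 0.97 |
| Skewed, some zeros | 11.9, 13.7 | 1.00 | 0.82 |
| Skewed | 19.9, 18.6 | 0.98 | 0.48 |
| Skewed, extra floor | 19.7, 19.1 | 0.97 | 0.36 |
| Mildly skewed | 20.0, 14.2 | 0.89 | 0.20 |
| Normal clipped at 0 | 21.4, 16.7 | 0.44 | 0.01 |
| Near-normal, as at six weeks | 40.2, 18.7 | 0.08 | 0.00 |

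A switch is likely with the corrected test and a skewed score. Otherwise it is uncertain.

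**4. Ranks against means at equal means, without the gate.** Assumptions: about 30 per arm and one-year means of about 12 in both arms. A share p of the three-week arm does badly and the five-week arm has no such subgroup. With poor scores averaging 50, the remainder must average (12 − 50p) / (1 − p): 8.92 at p = 0.075 and 5.29 at p = 0.15. The table gives the share of trials significantly favouring the short cast, as ranges over several runs with somewhat different shapes:

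| Poor outcomes, three-week arm only | Mann–Whitney | t-test |
|---|---|---|
| None (identical distributions) | 2.3–2.5% | 2.2–2.5% |
| 7–7.5% | 6–7% | 3–4% |
| 15% | 23–26% | 3.5–4.5% |

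**5. Adding the gate.** Four visits, within-patient correlation 0.5, 30 per arm. The gate counts as passed if the treatment effect or its interaction with time is significant. The last two columns give the share of trials in which Mann–Whitney favours the short cast:

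| Scenario | One-year means, 3 v 5 weeks | Gate passed | Without gate | With gate |
|---|---|---|---|---|
| Identical distributions | 11.9 v 11.9 | 8.7% | 2.8% | 1.0% |
| 10% poor, no earlier difference | 11.2 v 11.9 | 9.4% | 15.5% | 3.1% |
| 15% poor, no earlier difference | 12.1 v 11.8 | 9.3% | 25.6% | 3.6% |
| 12% poor, real early benefit | 11.4 v 11.9 | 83.2% | 27.0% | 24.0% |

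The early benefit was set at 14 points at six weeks and 8 points at three months. If the gate requires the treatment main effect alone, the last column is 2.2–2.6% for the two scenarios without an early difference and 19.6% for the early-benefit one.

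**The case against.** The strongest reply is that the rank test is not the main analysis. The stated analysis of function is an ANOVA on means, and no visit is compared until it is significant. This stands. A reader might infer that one-year QuickDASH will probably be judged by ranks, or that the short cast would be wrongly favoured in about a quarter of trials. The document supports neither. The first ignores the gate and depends on a distribution the article does not give and on a test version it does not specify. The second needs 15% poor outcomes in one arm and none in the other.

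The scenario can also be challenged. The Background's 7% to 8% is displacement after two weeks among radial fractures in general. It is not an excess caused by stopping at three weeks in fractures that need no reduction. The same section calls three weeks apparently safe and cites two trials of three against five weeks with no significant difference. With 7.5% poor outcomes in one arm and 3.75% in the other, the ungated contrast is only 4.2% against 2.7%. This stands too: at such rates the effect is small.

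Finally, a poor subgroup would not be hidden. Dislocation, complex regional pain syndrome and mal- or non-union are separate secondary outcomes, and means are shown whichever test is used. That is true, but the reader would then face a p-value and an estimate that may disagree, with no rule for which prevails.

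One part of the defence is weaker than it looks. The gate protects little if the short cast truly helps early. The Background says that shorter immobilisation could speed recovery, and the abstract expects it to be beneficial.

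**Conclusion.** The point holds in a limited form. The text lets a normality test on the outcome data decide, after the ANOVA gate, whether the one-year comparison concerns means or ranks. Sizing and reporting are on means. That mismatch follows from the wording and needs no simulation.

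How often it would matter rests on assumed distributions. When the arms have identical distributions there is no excess. When they differ in shape at equal means, the ungated excess is about 6% against 4% with 7.5% poor outcomes in the three-week arm only, and about 25% against 4% with 15%. With 10–15% poor outcomes the gate brings the rank figure down to 3–4%, or leaves it at about 24% if there is a real early benefit. In that last case a significant overall test is deserved, but a one-year claim could still mislead.

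The ANOVA should not be called invalid by the plan's own standard, since nothing in the text says so. Nor is it a finding that the article leaves open the test version, or whether testing is pooled, per arm or per visit. An analysis plan may settle these. The change is worth making because it costs almost nothing.

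**What to change.** In Univariate analysis:

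- Drop the Kolmogorov–Smirnov test as a rule for choosing the comparison. Skew may still be described.
- Name one primary contrast: the between-arm difference in mean QuickDASH at one year with its 95% confidence interval, using Welch, robust or bootstrap standard errors, whatever the normality result.
- Treat the other visits as secondary. The repeated-measures test can stay in front of them, so that no set of unguarded comparisons opens up.
- Report Mann–Whitney at one year as a sensitivity analysis that cannot replace the primary result.

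The cost is a reworded paragraph and a few lines of code, with no extra patients, visits or data. The downside is a possible small loss of power against a rank test if scores are skewed and the arms differ by a simple shift.

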### Ethical considerations

#### *Regulation statement*

The study was approved by the Regional Ethical Committee and will be carried out in compliance with the Declaration of Helsinki on ethical principles for medical research involving human subjects [20]. The Medical Ethics Committee Noord-Holland acts as central ethics committee for this trial (reference number M011-059; NL38449.09.11).

### Recruitment and consent

Patients with a distal radial fracture will be treated by the physician on call in the Emergency Department. The only difference is that duration of immobilization will be decided after randomization. Randomization will occur after informed consent.

### Administrative aspects and publication

#### *Handling and storage of data and documents*

The data will be coded by patient number. Research data will be stored in a database (PASW statistics 18 and Microsoft Excel), and will be handled confidentially and anonymously. Research data that can be traced to individual persons can only be viewed by authorized personnel. These persons are the members of the research team, members of the health care inspection, and members of the Medical Ethics Committee of the Academic Medical Center Amsterdam. Review of the data may be necessary to ensure the reliability and quality of the research. The handling of personal data is in compliance with the Dutch Data Protection Act (in Dutch: ‘Wet Bescherming Persoonsgegevens’, WBP) and the privacy regulation of the Academic Medical Center Amsterdam.

## Discussion

The duration of cast-immobilization for distal radial fractures remains a topic of debate. Currently, the decision for the duration of immobilization of distal radial fractures is predominantly based upon the personal preferences of the treating physician. The studies done for assessing the immobilization periods of distal radial fractures have their limitations of using a non-validated outcome score list, which makes it impossible to conclude with certainty shorter immobilization periods of distal radial fractures are preferred. Considering this statements, a new randomized trial with sufficient power is needed to provide evidence for a definitive, generally acceptable guideline for the treatment of non-displaced distal radial fractures. The results of this study will help to clarify the question if shorter periods of immobilizations are favorable in adult patients with conservatively treated distal radial fractures, thereby considering functional outcome, pain scores, incidence of non-union, and complications.
